The first trial tested the safety and immunogenicity of the mixture of three antigens given at a single site or given separately at three sites. For the first vaccination, volunteers received 3 x 100 g of antigen or 3 x 50 g; all received 3 x 20 g in the second vaccination. In the second trial, which compared the safety and immunogenicity of different doses of a mixture of the three antigens, the subjects received 3 x 50 g, 3 x 13 g or 3 x 4 g for the first vaccination and 3 x 20 g, 3 x 13 g or 3 x 4 g for the second vaccination, respectively. No serious adverse events were reported in either trial but local reactions, particularly pain and tenderness, occurred in the majority of subjects, These reactions lasted for up to a few days and were also seen in subjects receiving the adjuvant alone. One subject had a local reaction that was severe for three days before resolving gradually over three weeks.

In both trials some subjects had delayed local reactions with pain, tenderness and/or swelling developing 10 days or later after vaccination. These reactions were clearly related to antigen dose with the majority occurring in subjects receiving the mixture of 3 x 100 g antigen in a single site and none occurring in subjects receiving the lowest antigen dose or the adjuvant alone. The delayed reactions were mild to moderate in all but two subjects. One developed severe pain and swelling in the injected thigh 10 days after the vaccination, which resolved over a week. This subject was given 20 g of each antigen as a second vaccination and six weeks later developed a hard painful mass at the second injection site. The pain and the mass resolved over a few weeks with no biochemical evidence of muscle damage. The other with a severe delayed reaction developed pain and swelling in the thigh and around the knee two weeks after vaccination. There was marked discomfort on use. Symptoms resolved over two weeks with no biochemical evidence of muscle damage.

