The most common adverse event observed in trials using Montanide ISA720 is local reactogenicity (34). The acute reactions are characterized by of pain, swelling, induration, sterile abscess, and granuloma formation. These have been generally mild to moderate in 33 to 91% of volunteers. In the single Phase 2 trial in children in an endemic area the rate was 12% (26). The overall rate for mild and moderate acute local reactions is similar to that observed with licensed pediatric vaccines such as DT (standard pediatric dose) (55% mild/moderate local reactions) or dT (low dose vaccine) (52% mild/moderate reactions) in 6-year-old children. Severe local reactions occurred only with 5 vaccinees who received the vaccine via the intramuscular route for a cumulative rate of 1%. This proportion is not greater than that observed for some licensed vaccines (17% severe local reactions with DT and 11% severe local reactions with dT) (35). Severe local reactions were seen much more commonly in trials administering the vaccine subcutaneously. In these 2 trials (30) up to 44% of recipients of higher doses were not revaccinated due to local reactions. Acute local reactions were seen frequently with pain, swelling and/or induration most common. In the HIV vaccine study (33) sterile abscess and granuloma formation was seen in some volunteers, particularly those receiving the high antigen dose (2 mg), which was far in excess of that given in the malaria vaccine studies or that planned in this study. In most studies the vaccine was injected intramuscularly and when this route was used the majority of local reactions were mild to moderate with a cumulative rate of 1% for severe reactions. In contrast, severe local reactions were seen more commonly in the two studies in which the vaccine was administered subcutaneously (31, 32).

Delayed local reactions as seen in the Combination B studies (see Section 2.3.2) occurred in some volunteers in the majority of other trials with antigens formulated in Montanide® ISA720. Over all of the studies approximately 11% of volunteers developed these reactions, which were characterized by pain and swelling at the injection site occurring 10-28 days after vaccination. They resolved without sequelae usually in a few days but in some cases several weeks. There was a trend indicating that the rate and severity of these delayed reactions was increased with higher antigen doses and multiple injections.

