### 9.1.2 Analyses for Primary Objective (safety)

To assess the safety and tolerability of three immunisations at two dosage levels of the MSP2-C1/ISA720 vaccine in healthy malaria-naive volunteers

The incidence of AE and SAEs will be tabulated by treatment group (with the pooled ISA720 Control patients representing one group), System Organ Class and Preferred Term. Incidence in each treatment group will be compared with that in the pooled ISA720 Control group using Fisher's exact test (correcting for multiple comparisons across AEs using Holm's method (37). Separate assessments of systemic and local reactions will be performed. The overall number and percentage of volunteers with at least one AE (and SAE) will be tabulated after each vaccination and over the entire study period. In addition, longitudinal comparisons will be made for each treatment group using Lidell’s exact version of McNemar’s test. The incidence, intensity, and relatedness to vaccination of individual symptoms will be calculated for each dose and study arm. The incidence, intensity and relatedness to vaccination will be calculated for each treatment group.

If any clinically significant deviations from normal occur in routine laboratory test results and/or vital signs, they will be analyzed using a longitudinal linear mixed model, with Treatment Group and Time as fixed effects, and subject and times within subject as random effects. An appropriate covariance structure will be selected for the longitudinal error term. These analyses will be repeated for change from baseline values, where the baseline is given by pre-dose values.

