Appendix 2 - Assessment of Adverse Event Severity

| **Adverse Event** | **Grade** | **Intensity** |
| --- | --- | --- |
| Pain at injection site | 0 | Absent |
|  | 1 | Pain that is easily tolerated |
|  | 2 | Pain that interferes with daily activity |
|  | 3 | Pain that prevents daily activity |
| Erythema at injection site | 0 | 0 mm |
|  | 1 | >0 - <20 mm |
|  | 2 | >20 - <50 mm |
|  | 3 | >50 mm |
| Swelling at injection site | 0 | 0 mm |
|  | 1 | >0 - <20 mm |
|  | 2 | >20 - <50 mm |
|  | 3 | >50 mm |
| Induration at injection site | 0 | 0 mm |
|  | 1 | >0 - <20 mm |
|  | 2 | >20 - <50 mm |
|  | 3 | >50 mm |
| Fever (oral) | 0 | <37.5°C |
|  | 1 | 37.6°C - 38.0°C |
|  | 2 | >38.0°C – 39.0°C |
|  | 3 | >39.0°C |
| Headache | 0 | None |
|  | 1 | Headache that is easily tolerated |
|  | 2 | Headache that interferes with daily activity |
|  | 3 | Headache that prevents daily activity |
| Nausea | 0 | None |
|  | 1 | Nausea that is easily tolerated |
|  | 2 | Nausea that interferes with daily activity |
|  | 3 | Nausea that prevents daily activity |
| Malaise | 0 | None |
|  | 1 | Malaise that is easily tolerated |
|  | 2 | Malaise that interferes with daily activity |
|  | 3 | Malaise that prevents daily activity |
| Myalgia | 0 | None |
|  | 1 | Myalgia that is easily tolerated |
|  | 2 | Myalgia that interferes with daily activity |
|  | 3 | Myalgia that prevents daily activity |
| Arthralgia | 0 | None |
|  | 1 | Joint pain that is easily tolerated |
|  | 2 | Joint pain that interferes with daily activity |
|  | 3 | Joint pain that prevents daily activity |
| Urticaria | 0 | None |
|  | 1 | Requiring no medications |
|  | 2 | Requiring PO or topical treatment or IV medication or steroids for <24 hours |
|  | 3 | Requiring IV medication or steroids for >24 hours |

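### The formal adverse-event tests in section 9.1.2 use only yes/no outcomes, so for common local reactions the within-group McNemar test has little room to show worsening across injections; the 0-3 grades already collected could be tested instead

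*Protocol*

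**What the plan says.** Section 9.1.2 names two tests for adverse events. Between groups: "Incidence in each treatment group will be compared with that in the pooled ISA720 Control group using Fisher's exact test", with Holm's correction across events. Within groups: "longitudinal comparisons will be made for each treatment group using" the exact McNemar test. The outcome for the second test is not spelled out, but the sentence before it gives a yes/no measure: "The overall number and percentage of volunteers with at least one AE (and SAE) will be tabulated after each vaccination". Intensity is to be calculated by dose and arm, and no test or model uses it. The mixed model in the same section covers laboratory values and vital signs only.

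Appendix 2 grades each solicited reaction from 0 to 3; for injection-site pain, for instance, Grade 2 is "Pain that interferes with daily activity".

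On acute local reactions with this adjuvant, section 2.3.3 says: "These have been generally mild to moderate in 33 to 91% of volunteers". Section 2.3.2 reports them in more than half of the subjects of earlier trials of a vaccine containing MSP2, and section 2.3.3 reports them in most subjects after the first dose of a three-dose trial with the same adjuvant. Section 2.3.2 adds that they "were also seen in subjects receiving the adjuvant alone", without a rate.

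**The concern.** The primary objective is the safety and tolerability of three injections at two dose levels. Whether reactions get worse from one injection to the next is therefore a central question, and McNemar is the test assigned to it.

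If most volunteers already react to the first injection, presence or absence has almost nowhere to go. What can still change is the grade, and the planned test discards it. A result of no significant change across injections could then be read as reassurance although many volunteers had moved from mild to moderate or severe. This loss exists in a single unadjusted comparison, so it is separate from any cost of the Holm correction.

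**Working it through.** **Inputs.** 12 vaccinees per dose group (sections 3.2 and 9.1.4). Pooled control 2 x 3 = 6 (section 3.2; section 9.1.4 says 9, which does not fit two cohorts). Incidence 33-91% (section 2.3.3). Section 9.1.2 states no significance level, so two-sided 5% is assumed, with 10% alongside. All 12 are assumed to receive both injections compared; with fewer, the limits below are lower.

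**The plan's own figure.** The only power statement is 0.80 in section 9.1.4, for seeing at least one event of probability 0.15. With n = 12 this is 1 - 0.85^12 = 0.858, so 0.80 is not reproduced (n = 10 gives 0.803). It does not concern Fisher or McNemar.

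**Upper limit on McNemar.** With d discordant pairs all in one direction, p = 2 x 0.5^d. Five give 0.0625 and six give 0.031, so a significant increase needs at least six volunteers who newly react. They can come only from those without a reaction at the first injection. Whatever the true effect, power for an increase is at most P(Bin(12, 1 - incidence) >= 6). At the 10% level the requirement is five.

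| Incidence at first injection | Limit at 5% | Limit at 10% |
|---|---|---|
| 33% | 94% | 98% |
| 50% | 61% | 81% |
| 60% | 33% | 56% |
| 70% | 12% | 28% |
| 75% | 5.4% | 16% |
| 80% | 1.9% | 7% |
| 91% | 0.03% | 0.3% |

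Reaching the limit requires every volunteer to react at the later injection. For a rise from 50% to 75%, exact power is only 5-10%.

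**What the grades would add (assumed distributions).** The protocol gives no grade distribution, so these are illustrations for n = 12 at the 5% level, by simulation. Grades 0/1/2/3 start at 20/60/15/5%. The ranges cover within-subject correlation 0 to 0.8.

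| Later injection | McNemar, any grade | McNemar, Grade >=2 | Exact signed-rank |
|---|---|---|---|
| 10/20/40/30% | 0.1-0.7% | 50-61% | 50-88% |
| 20/20/40/20% | 0-0.3% | 30-33% | 21-42% |
| unchanged | under 1% | under 1% | under 2% |

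In a second model (normal latent severity, shift of 1 SD, correlation 0.5, assumed grade cut-points), signed-rank had 58-65% power across 33-91% incidence, against 0-31% for any-grade McNemar and 11-30% for McNemar with a Grade >=2 cut. At a shift of 0.5 SD signed-rank had only 5-17%.

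**Between groups.** If all 12 vaccinees react, Fisher gives p = 0.025 against 3/6 controls, 0.098 against 4/6, 0.33 against 5/6 and 1.0 against 6/6, before Holm. With 100% of vaccinees reacting, power is 90% at a 33% control rate, 66% at 50%, 26% at 70% and 10% at 80%. For a 1 SD shift, Wilcoxon-Mann-Whitney on grade against Fisher gives 35-37% against 23%, 11% and 1% at control rates of 50%, 75% and 91%, but only 29% against 25% at 33%, and 21% against 20% at 20%.

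**The case against.** Several points on the other side stand.

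- **Controls.** A reader might infer that the protocol expects most adjuvant-only controls to react. It does not say so: reactions were seen in them, no rate is given, and section 2.3.3 calls the adjuvant alone well tolerated. The ceiling on Fisher is therefore conditional.
- **Severity.** A reader might also take "the rate and severity of these delayed reactions was increased with higher antigen doses and multiple injections" as a forecast for local reactions generally. The sentence reports a trend for delayed reactions, which occurred in about 11% of volunteers and are not near a ceiling. For acute reactions the protocol describes no escalation of grade and puts severe ones at about 1% by the intramuscular route.
- **Unit of analysis.** The 33-91% is for acute local reactions taken together. Single terms such as erythema will be less common, and systemic reactions occurred in a minority. At 33% the McNemar limit is 94%, so a very large rise could be detected.
- **Visibility.** Worsening would not go unseen. Intensity tables and individual graphs (section 9.1.1) are planned, and the hold criteria in section 7.5 use grade. What is missing is a formal test.
- **Outcome left open.** Section 9.1.2 does not define the McNemar outcome, and the analysis plan, which is not at hand, could apply a Grade >=2 cut. That recovers much of the power and in one illustration matches signed-rank or does slightly better. It is still one yes/no cut, and nothing in section 9.1.2 states it.

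The limit on any-grade McNemar is not touched by these points. Section 9.1.1 commits to significance testing as well as description, and section 9.1.2 names the tests itself, so this is not a detail left for later.

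**Conclusion.** The point holds for common acute local reactions compared between injections within a dose group. At about 50% incidence or more, the planned McNemar test on presence or absence can hardly show an increase: at most 61% power at 50%, 12% at 70%, 5% at 75% and 0.03% at 91%. It cannot register a change of grade at any incidence. These limits are exact and assume n = 12, a two-sided 5% level and an any-grade outcome.

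The size of the gain from using grades is less certain, since it rests on an assumed grade distribution, shift and correlation. It is large against an any-grade McNemar and smaller or absent against a Grade >=2 cut. Against control, the gain depends on an unstated reaction rate and is small when that rate is about 33% or less. The documents do not support extending the point to delayed reactions, rare events or all adverse events. This is a cheap improvement to the analysis, not a flaw that would hide harm.

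**What to change.** In section 9.1.2, keep the incidence tables, confidence intervals, Fisher and McNemar, and state the outcome to which McNemar applies. For the solicited local reactions of Appendix 2 that are expected to be common, named in advance, make the within-group comparison between injections on each volunteer's maximum grade (0-3) after each injection, over a stated diary period, with an exact Wilcoxon signed-rank test. Add an exact Wilcoxon-Mann-Whitney test on maximum grade for each dose group against pooled control, with a note that its gain depends on the control reaction rate. State the significance level for these tests.

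The cost is a few sentences and a few lines of programming; the grades are already collected. The downsides are that a shift in grade is less direct to report than a difference in percentages, so the incidence table should stay beside it, and that power remains modest for small shifts. A non-significant result should still not be read as evidence of no worsening.

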### 9.1.3 Analyses for Secondary Objectives (Immunogenicity)

### 9.1.3.1 Characterise the humoral and cellular immune responses to the MSP2-C1/ISA720 vaccine:

Anti-MSP2 antibodies (anti-MSP2 3D7 & anti-MSP2 FC27- Total and Ig G subtype) will be measured by ELISA for each serum sample. Immunogenicity responses will be described by vaccine and dose group, over time. Individual responses will be described over time and stratified by dose cohort. Antibody titres will be measure on Days 0, 28, 84, 112, 168, 196, and 336). The primary immunogenicity endpoint will be evaluation of sera taken at 28 days after each vaccination, and at six months after the final vaccination as listed in the schedule of visits (Appendix 1).

Antibody responses will be analysed using a longitudinal linear mixed model, with MSP2 serotype, Dose and Time as fixed effects, and Subject and Times within Subject as random effects. An appropriate covariance structure will be selected for the longitudinal error term. Because of the small sample size of this study, statistical tests will be performed without correction for multiplicity. A nominal Type I error rate of 10 percent will be used. Parameter estimates will be obtained using the REML algorithm (38). Contrasts will be generated to evaluate MSP2 serotype and Dose effects at each time point. Formal statistical tests will assess whether the response is monotone (low dose < medium dose < high dose) for the 2 doses of vaccine being tested to look for a dose response.

The vaccine dose level which induces the highest concentrations of MSP2 specific IgG will be determined graphically.

Additionally, the cell mediated responses (T cell proliferation, cytokines) will be performed on Days 0, 28, 112, 196, and 336. T cell proliferation and cytokines will be analysed in the same way, using a longitudinal linear mixed model. Analyses will include (but not be limited to) contrasts to examine difference between MSP2 serotypes and Dose levels at each time point. All of these analyses will be repeated using pre vaccination (day 0) values as a covariate.

The following parameters will be summarised by simple descriptive statistics:

Parameter 1: The ability of the vaccine induced antibody to inhibit parasite growth as measured by the in vitro growth inhibition assay (GIA)

Parameter 2: The relationship between anti-MSP2 antibody levels and degree of in vitro parasite growth inhibition.

Graphs will display growth inhibition expressed as a percent of inhibition comparing test sera to pre-immune sera. Depending on the distribution of the data, parametric or non-parametric methods will be used to compare inhibition as a function of dose, and serotype.

Should the need arise for terminating the study early, the investigative team will discuss with the SMC the reason for termination and determine which study questions can be addressed in an unbiased manner with the available data. The available data will be analyzed and interpreted in light of early termination. Deviations from the statistical plan will be reported in the study report.

### 9.1.4 Sample Size

This study is powered to provide sufficient safety data on an adult population living in an area without malaria. A group size of 12 volunteers per dose will receive the MSP2-C1/ISA720 malaria vaccine and a total of 9 participants, 3 per dose cohort will receive ISA 720 Control vaccine as a control. This will give a probability of 0.80 for detecting one or more serious or severe AEs that occurred with a probability of 0.15 per volunteer.

# 10.0 Protection of Human Subjects

## 10.1 Institutional Review Board/Human Research Ethics Committee

The study will be conducted in accordance with the principles of the Declaration of Helsinki (Recommendations guiding Medical Doctors in Biomedical Research Involving Human Subjects), and with the NH&MRC National Statement on Ethical Conduct in Research Involving Humans (2007). The conduct of the study will be in accordance with the Notes for Guidance on Good Clinical Practice (CPMP/ICH/135/95), as adopted by the Australian Therapeutic Goods Administration (2000).

The Investigator will be responsible for obtaining IRB/HREC approval for the study. Before the start of the study, the appropriate documents (including the Protocol, Investigator’s Brochure, Informed Consent Form, information sheets, Diary Cards and advertisements) will be submitted to the IRBs/HRECs. A copy of the study approval (including approval of the informed consent form) is to be maintained in the Investigator’s study document binder and a copy will be supplied to the Sponsor. During the study, the Investigator is responsible for providing the IRB/HRECs with all documents subject to review (i.e., Protocol Amendments, informed consent form updates, advertisements, and any written information that may be provided to the subject). Annual reports on the progress of the study will be made to the IRBs/HRECs by the Investigator in accordance with IRB/HREC guidelines and government regulations.

## 10.2 Informed Consent

In obtaining and documenting informed consent, the Investigator must comply with the applicable regulatory requirements, Good Clinical Practices, ICH Guidelines, and ethical principles. The written informed consent form must be approved by all IRBs/HRECs prior to its use.

Participants will be fully informed of the nature of the study, the properties and side effects of the investigational products, and all relevant aspects of study procedures. Subject information is provided predominantly by a Medical Investigator during recruitment. Participants will receive a copy of the ‘Privacy Information and Informed Consent Form for Screening’ (Appendix 5) and the ‘Information for Volunteers and Consent Form for Study Participation’ (Appendix 6). They may ask questions of a Medical Investigator or the Clinic Staff at any time.

The recruitment procedures consent form will be signed and dated by the volunteers in the presence of an investigator. The study participation consent form will be signed and dated by the volunteers in the presence of an investigator.

## 10.3 Risks

Risks to the volunteers are associated with venipuncture and with immunisation. These risks are outlined below.

Female participants will be counseled on the unknown risk of the MSP2-C1/ISA720 vaccine to the foetus and will be advised to use adequate birth control methods from screening through the entire trial duration. Any female participant interested in contraceptive methods will be referred to the local health center or family planning services for evaluation and institution of an appropriate contraceptive method.

### 10.3.1 Venipuncture

Risks occasionally associated with venipuncture include pain and bruising at the site of venipuncture, lightheadedness, and syncope (rarely). Volunteers will be advised not to donate blood during the study and for 30 days after the study ends.

### 10.3.2 Immunisation

Possible local vaccine reactions include pain, swelling, erythema, induration, nodule formation, limitation of limb movement for several days, lymphadenopathy, or pruritis at the injection site. Delayed type local injection site reactions may be seen with the Montanide® ISA720 adjuvant. Systemic reactions such as fever, chills, headache, fatigue, malaise, myalgia and joint pain may also possibly occur. Immediate hypersensitivity reactions including urticaria, anaphylaxis or other IgE mediated responses are possible as with any vaccine. As with any investigational vaccine, there is a theoretical possibility of risks about which we have no present knowledge. Volunteers will be informed of any such risks should further data become available.

